### Participant timeline {13}

A study flowchart is provided in Fig. 3.

**Fig. 3 Fig3:**
[figure not shown]
Study flowchart

### Sample size {14}

Sample size calculations were conducted using G*Power [71]. The sample size calculation was based on a power of 0.8 and a *p* value of 0.025 as there are two primary outcomes. Two-sided *t*-tests were used as the basis for the analysis, and a meaningful group difference of 12% for QOLIBRI (pooled SD 20%), and a difference of 1.8 for the Part-O (pooled SD 3), were assumed. With this, 54 patients would be required in each group. With an assumed attrition rate of 10% at T3, 60 participants will be included in each intervention arm.

### Recruitment {15}

Potentially eligible participants will be invited by letter and screened by phone for inclusion and exclusion criteria. Eligibility will be confirmed at baseline assessment before participants are randomized. Potential participants will be recruited from previous research studies conducted at OUH and, if necessary, from the outpatient TBI department at OUH and Sunnaas Rehabilitation Hospital to reach the target sample size.

### Assignment of interventions: allocation

#### Sequence generation {16a}

Participants will be randomly allocated in a 1:1 ratio to either group. A web-based block randomization will be generated by an independent statistician prior to trial start-up to ensure randomization and complete allocation concealment. Variable block size (generated by Stata version 15) will be applied.

#### Concealment mechanism {16b}

The allocation sequence will be stored in a database that can only be accessed by the study principal investigator (PI). Neither the therapists assigning participants to randomization nor the outcome assessors have access to this data base. The PI can only access the numbers sequentially.

### Assignment of interventions: Blinding

#### Who will be blinded {17a}

Blinding of the participants and therapists is not possible; however, the outcome assessments at T2 and T3 will be conducted by independent assessors blinded to participants’ group assignment. Researcher blinding during statistical analyses will be achieved by reassigning participant ID numbers. To further ensure blinding, an independent researcher will run the main analyses regarding between-group effects.

#### Procedure for unblinding if needed {17b}

There is no need for unblinding procedures in this trial.

### Data collection and management

#### Plans for assessment and collection of outcomes {18a}

Outcome assessors will be trained in the administration of all outcome measures. The estimated time for completion of the data collection is 3–5 h for T1 and 1–2 h for T2 and T3. Most questionnaires and semi-structured interviews used have been translated into Norwegian and validated in previous studies, with a few exceptions. The NPCS is currently being validated in Norwegian conditions. The acceptability scale and Quality of Relationships scale from Winter et al. were translated into Norwegian by our research group and have not yet been validated. Likewise, the Veteran’s In-home Programme Manual developed by Winter et al. was translated into Norwegian and adjusted to the Norwegian setting. The translated manual was evaluated in a feasibility study in which all sessions where conducted by two of the therapists together, ensuring adherence to the manual and reliability as well as identifying necessary adjustments to the Norwegian version before recruitment for the RCT.

#### Plans to promote participant retention and complete follow-up {18b}

One specific researcher has been assigned administrative responsibility for follow-up of all participants to ensure adherence to planned timing of follow-ups (T1, T2, and T3) in both the treatment and control group to ensure call-backs. Any deviation from the standard timing of outcome assessments due to practical or other reasons will be discussed in the study group.

### Data management {19}

All data material will be recorded with a participant ID and will be unidentifiable, and only the researchers working in the project group will have access to lists that link participant numbers with names. De-identified data will be electronically stored on the research server at OUH and will be deleted 5 years after the project has ended. The final dataset will be available to researchers actively contributing to statistical analyses and publications. Data entry will be controlled by initial exploratory analyses, including range checks and double data entry, in order to promote data quality.

### Confidentiality {27}

Information about participants will be handled by health-care professionals adhering to Norwegian law on confidentiality. Information that could contribute to breach of confidentiality will not be published without the express consent of the individuals in question. Data are stored in accordance with Norwegian Data Protection Law.

### Plans for collection, laboratory evaluation, and storage of biological specimens for genetic or molecular analysis in this trial or future use {33}

Not applicable.

### Statistical methods

#### Statistical methods for primary and secondary outcomes {20a}

Descriptive statistics will be used to depict demographics, injury characteristics, and service delivery at baseline as well as acceptability in the intervention group.

The effect of the intervention will be assessed by linear mixed-effect models fitting the primary outcome variables to account for repeated measurements by patients. Time and time-by-treatment interaction will be used as fixed effects in these models. The linear mixed model will give estimated mean values with 97.5% confidence intervals for all time points (T1, T2, and T3) for each group. Estimates of mean between group changes from T1 to T2 and T2 to T3 will also be provided. The analysis of primary interest in establishing treatment efficacy is a time × group interaction in the direction of the intervention group improving above the levels of the control group at T3. Due to two primary outcomes, a significance level of *p* < 0.025 will be applied.

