### Objectives {7}

Our specific hypotheses are:
H1: Person-centered intervention targeting the participant’s problems in functioning in their living environment will result in improved quality of life and participation compared with treatment as usual (TAU).H2: Person-centered intervention will result in a lower burden of self-reported TBI-related problems compared with TAU.H3: Person-centered intervention will result in improved physical and mental health compared with TAU.H4: Person-centered intervention will result in fewer unmet health-care needs compared with TAU.H5: Person-centered intervention will be a cost-effective alternative compared with TAU.H6: Patients, family members, and rehabilitation professionals involved will be satisfied with the intervention program.

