### Health economic analysis

To determine the cost-effectiveness if the intervention proves to be effective (i.e., at least a moderate effect size on one of the primary outcomes), a statistical analysis of costs will be performed. The total costs will be calculated by adding up direct health-care costs, direct non-health costs, and indirect costs. As the distribution of costs can be skewed, differences in costs between groups will be calculated by means of bootstrapping. A cost-utility analysis will relate the difference between the intervention and control group to changes in utility. This will result in costs per quality-adjusted life years (QALY). QALYs can be derived from the EQ-5D data. Standard discounting will be performed for both costs and outcomes together with sensitivity and uncertainty analyses to gain insight into the generalizability of the economic evaluation.

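### Testing each primary outcome at a fixed 0.025 is valid, but Holm's procedure gives more power at the same 5% family-wise error

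*Protocol article*

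**What the plan says.** The section on statistical methods for primary and secondary outcomes {20a} plans a linear mixed model for each primary outcome, with the time-by-group interaction at T3 as the test of interest and 97.5% confidence intervals. On multiplicity it states: "Due to two primary outcomes, a significance level of *p* < 0.025 will be applied". No step-down is described.

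The sample size section {14} uses the same level, with "a power of 0.8 and a *p* value of 0.025 as there are two primary outcomes". It adds that "Two-sided *t*-tests were used as the basis for the analysis" and gives a difference and SD for each outcome separately. The result is 54 evaluable patients per group, or 60 randomized per arm after 10% attrition.

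Two other places bear on what counts as success. In Objectives {7}, H1 predicts that the intervention "will result in improved quality of life and participation compared with treatment as usual (TAU"), joining the two outcomes with 'and'. The health economic section makes the cost-effectiveness analysis depend on "at least a moderate effect size on one of the primary outcomes".

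**The concern.** Splitting 5% equally between two outcomes is the standard rule when a claim may rest on either of them. For that purpose a fixed split is not the most efficient valid choice. Holm rejects everything the fixed split rejects, sometimes rejects one outcome more, and keeps the same family-wise error.

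The difference matters when one outcome is clearly positive and the other has a p-value between 0.025 and 0.05. Suppose QOLIBRI gives p = 0.001 and PART-O gives p = 0.035. The protocol's rule would declare no significant effect on participation. Holm would support both claims at the same 5% family-wise error. With 120 participants, a conclusion on one of the two primary outcomes could turn on this.

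There is also a matter of wording. H1 says 'and', the alpha split implies 'either', and 0.8 is not labelled as power per outcome. A reader could mistake which claim the 80% belongs to.

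**Working it through.** **Inputs (sample size section {14})**

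- QOLIBRI: difference 12, SD 20, so d = 12/20 = 0.60.
- PART-O: difference 1.8, SD 3, so d = 1.8/3 = 0.60.
- Two-sided alpha 0.025 per outcome; 54 evaluable per group; 10% attrition.
- Correlation ρ between the two test statistics: not given, so varied.

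**Step 1. Reproduce the plan's figure.** The noncentrality is d·√(n/2) = 0.6 × √27 = 3.118, with 2 × 54 − 2 = 106 degrees of freedom. The noncentral t distribution gives power 0.799 at alpha 0.025 and 0.871 at alpha 0.05. The normal approximation gives 53 per group. Attrition: 54/0.9 = 60. The stated 54 and 60 are therefore right, and 0.8 is the power for one outcome.

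**Step 2. Error rate under Holm.** If neither outcome has an effect, any false claim needs the smaller p-value to be at or below 0.025, which has probability at most 0.025 + 0.025 = 0.05. If exactly one outcome has no effect, claiming it needs its own p-value to be at or below 0.05. Family-wise error is at most 0.05 in every case.

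**Step 3. Power at ρ = 0.**

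- Both, fixed split: 0.799² = 0.639.
- Both, Holm (both at or below 0.05 and at least one at or below 0.025): 2 × 0.7993 × 0.8706 − 0.6389 = 0.753.
- At least one, either rule: 2 × 0.7993 − 0.6389 = 0.960. Holm's first step is the Bonferroni test, so this cannot change.
- Per outcome, Holm: (power for both + power for at least one)/2 = (0.753 + 0.960)/2 = 0.856, against 0.799 now.

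**Step 4. Other correlations.** The two statistics were taken as bivariate normal, with marginal powers matched to the noncentral t values in step 1.

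| Assumed ρ | Both, fixed 0.025 | Both, Holm | At least one (same under both rules) | Per outcome, fixed | Per outcome, Holm |
|---|---|---|---|---|---|
| 0 | 63.9% | 75.3% | 96.0% | 79.9% | 85.6% |
| 0.3 | 66.5% | 76.7% | 93.3% | 79.9% | 85.0% |
| 0.5 | 68.6% | 78.0% | 91.2% | 79.9% | 84.6% |
| 0.7 | 71.2% | 79.6% | 88.7% | 79.9% | 84.1% |
| 0.9 | 74.9% | 81.5% | 84.9% | 79.9% | 83.2% |

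For ρ from 0 to 0.7, Holm adds 75.3 − 63.9 = 11.4 points down to 79.6 − 71.2 = 8.4 points for showing both. Per outcome it adds 85.6 − 79.9 = 5.7 points down to 84.1 − 79.9 = 4.2 points.

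**The case against.** The best defence is that Bonferroni is a valid prespecified rule and is applied consistently: the sample size, the test level and the 97.5% intervals all match. A more powerful alternative does not turn it into an error. All of that stands, and it is why this is an improvement to make and not a mistake to correct.

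A reader might go further and infer that the trial is underpowered, with only 64–71% power for H1 instead of 80%. The documents do not support that.

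- No section says both outcomes must be significant. H1 is a scientific hypothesis naming two outcomes; the decision rule is the alpha split, which would not be needed if both were required. In that case each could be tested at 0.05, giving about 76% power at ρ = 0 and 81% at ρ = 0.7.
- The sample size section gives a separate effect and SD for each outcome and claims no joint power.
- The 'one of' wording in the health economic section fits an either-outcome reading. It is only an effect-size trigger for the cost analysis, however, and not a significance rule.

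Under the either-outcome reading, power to show at least one effect is already about 89–96% for ρ from 0.7 to 0.

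It can also be said that a statistical analysis plan, not shown here, might add a step-down. That does not dispose of the point: the protocol does not leave the rule open but fixes 0.025 for both outcomes, so a different rule elsewhere would conflict with it.

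Finally, an outcome that misses 0.025 is not lost from the report, because estimates and intervals are given whatever the p-value. What is lost is the confirmatory claim.

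**Conclusion.** The point holds as one of efficiency and clarity. The fixed 0.025 rule controls the error rate and the stated sample size is right, but Holm does at least as well in every case, with no more patients and no loss of family-wise error control. At the planned effects, power per outcome rises from 0.80 to about 0.84–0.86, power to show both rises from about 64–71% to about 75–80%, and power to show at least one is unchanged.

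These figures rest on four assumptions: true effects of d = 0.6 on both outcomes; 54 evaluable patients per group; a correlation of 0 to 0.7, which is mine because the protocol gives none; and a two-sample t-test, as in the sample size section. The planned repeated-measures mixed model may have different power. The gain arises only when the other outcome passes 0.025, so it shrinks if just one outcome truly responds, but it is never negative.

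**What to change.** 1. In the statistical methods section {20a}, replace the fixed level with Holm's procedure: compare the smaller of the two primary p-values with 0.025; if it is significant, compare the other with 0.05; otherwise stop.
2. In Objectives {7}, reword H1 to quality of life 'and/or' participation, so that it matches the either-outcome alpha split.
3. In the sample size section {14}, label 0.8 as power per outcome.
4. Keep the 97.5% intervals as the conservative simultaneous ones, and show a 95% interval beside them for the outcome tested second.

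The cost is a few sentences, plus an amendment through the route the protocol already describes (the Data Protection Office and the trial registry), made before any between-group results are seen. The sample size stays the same. The only statistical downside is the one that item 4 handles: the 97.5% interval does not correspond to the second Holm test.

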#### Methods for additional analyses (e.g., subgroup analyses) {20b}

Individual and treatment-related predictors for goal attainment will be assessed by multivariable regression analysis in the intervention group. Intention-to-treat analyses will be performed in all analyses adjusted for sociodemographic and service-content variables from the ICSO-R.

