### Trial design {8}

The study is a two-group RCT with a mixed-methods design. Figure 1 displays standard protocol items according to the Standard Protocol Items: Recommendations for Interventional Trials (SPIRIT) [34, 35]. Potentially eligible participants will be invited by letter and screened by phone for inclusion and exclusion criteria. A baseline assessment (T1) will be conducted using measures of cognitive, emotional, and physical functioning as well as functional competence, participation, current use of health-care services, and main activity problems. Subsequently, participants will be randomized to intervention or TAU groups. Further assessments will be carried out 4–5 (T2) and 12 months (T3) after baseline. The timing of the T2 assessment will be aimed to correspond to the approximate end of the intervention for the intervention group. Use of health-care services will be registered and mapped according to the International Classification System for Service Organization in Health-related Rehabilitation (ICSO-R) [36] over the study period in both groups.

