When relevant and feasible, family members or local health professionals who are involved in the care of the participants will be invited to participate during the intervention sessions. At baseline assessment, participants can nominate their primary local health-care professional to join the intervention sessions if they wish. For participants without a local health-care professional but considered to be in need of establishing contact with primary care services, the therapist will establish such contact in collaboration with the patient’s general practitioner to ensure lasting knowledge transference.

Four therapists (a psychologist, neuropsychologist, physician, and physiotherapist) will be responsible for the delivery of the intervention.

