##### Treatment as usual

The control group will continue to receive their usual health-care and rehabilitation services provided in the municipality. In Norway, the municipalities are mainly responsible for follow-up in the chronic phase of TBI. This follow-up will potentially vary greatly depending on the needs of the individual and what municipality they live in, ranging from no follow-up to regular contact with local rehabilitation teams. The services provided for each individual in the control group will be thoroughly logged at all follow-ups to allow comparison with the intervention group regarding content, professionals involved, etc. Any concurrent treatment of this type will not be discontinued in any group due to ethical considerations.

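### The rule adjusting all analyses for ICSO-R service content is not limited to pre-randomisation values, so it permits adjustment for services that the intervention may change

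*Protocol article*

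**What the plan says.** The adjustment rule is the last sentence of the section on additional analyses {20b}: "Intention-to-treat analyses will be performed in all analyses adjusted for sociodemographic and service-content variables from the ICSO-R". It does not say at which visit the service variables are taken.

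Other sections bear on what those variables are:

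- **Trial design {8}** has health-care use registered and mapped under the classification ("ICSO-R) [36] over the study period in both groups"). The same section lists "current use of health-care services, and main activity problems" among the T1 measures, and T1 precedes randomisation.
- **Treatment as usual** states: "The services provided for each individual in the control group will be thoroughly logged at all follow-ups". The stated purpose is to compare care between the groups.
- **Intervention description {11a}** says that, for participants without a local professional but "considered to be in need of establishing contact with primary care services, the therapist will establish such contact".
- **Objectives {7}**, H4: "Person-centered intervention will result in fewer unmet health-care needs compared with TAU".
- **Statistical methods for primary and secondary outcomes {20a}** describes the mixed model for the primary outcomes: "Time and time-by-treatment interaction will be used as fixed effects in these models". It names no covariates. It also mentions a descriptive summary of services at baseline.

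**The concern.** An intention-to-treat comparison keeps the protection of randomisation only if the adjustment variables cannot have been affected by allocation. Service content recorded after randomisation may not meet that condition here, because arranging services is one thing the therapists may do.

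Two distortions follow if such values enter the model. If better services are one route by which the programme helps, adjusting for them removes that part of the effect. If participants with more severe problems both use more services and do worse, adjustment makes the arms differ in severity at any given level of service use, and can create a difference that is not there. In either case the coefficient is no longer the effect of being assigned to the programme.

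The phrase covering all analyses raises a second question: whether the rule reaches the primary model, which is described without covariates.

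**Working it through.** **Step 1. The planned effect.** Inputs from Sample size {14}: differences of 12 (SD 20) for QOLIBRI and 1.8 (SD 3) for PART-O, two-sided alpha 0.025, power 0.80. Both give d = 12/20 = 1.8/3 = 0.6.

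- Normal approximation: n = 2(2.241 + 0.842)²/0.6² = 52.8, so 53 per group.
- Exact t-test: 54.08, with power 0.799 at 54 per group.
- Attrition: 54/0.90 = 60 per arm.

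The plan's 54 and 60 are reproduced. They rest on a plain group difference of 0.6 SD with no service adjustment.

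**Step 2. What the text permits.**

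| Question | What the article supports |
|---|---|
| When are ICSO-R data recorded? | Over the study period, so including after randomisation |
| Are services logged at follow-up? | Yes, stated for the control group at all follow-ups |
| Is there pre-randomisation service information? | Yes, at T1 |
| Does {20b} restrict the adjustment to T1? | No |
| Can the intervention alter services? | By design, for a share of participants that is not given |
| Does {20a} list service covariates? | No |

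Post-randomisation adjustment is therefore permitted but not expressly prescribed.

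**Step 3. Direction of the bias.** Take one service variable S with within-arm SD 1, a treatment shift in S of a SD, and a within-arm slope β of outcome on S. In a linear model at one visit:

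adjusted effect = total effect − a × β

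A pre-randomisation S has a = 0 in expectation, so there is no bias. For a post-randomisation S, the sign depends on β. The documents give neither a nor β, so every value below is an assumption.

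- *Mediation only* (services improve outcome by b SD per SD, so β = b). With a = 0.3 to 0.8 and b = 0.1 to 0.3, the loss is a × b = 0.3 × 0.1 = 0.03 SD up to 0.8 × 0.3 = 0.24 SD. That is 5% to 40% of 0.6 SD, or 0.6 to 4.8 QOLIBRI points (× 20) and 0.09 to 0.72 PART-O points (× 3).
- *Severity only* (an unmeasured factor raises service use and lowers outcome, each with loading c, so β = −c²). With a = 0.25 to 1.0 and c = 0.3 to 0.5, a true null appears as a × c² = 0.25 × 0.09 = 0.0225 SD up to 1.0 × 0.25 = 0.25 SD in favour of the intervention. That is 0.45 to 5.0 QOLIBRI points. A simulation of 400,000 participants per setting agreed (0.02 to 0.255 SD adjusted), while the unadjusted contrast stayed within 0.006 SD of zero.
- *Both together*: β = b − c². With b = 0.3 and c = 0.3, β = +0.21 and the effect is understated. With b = 0.1 and c = 0.5, β = −0.15 and it is overstated. Even within these ranges the sign is undetermined.

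**The case against.** The best defence is that the sentence is loosely worded rather than wrong. Service use is taken at T1, the descriptive analysis mentions baseline services, and {20b} pairs the service variables with sociodemographic ones, which are baseline variables. Follow-up logging has a stated descriptive purpose, and no section says that follow-up values enter an outcome model. A condensed article may leave the covariate list to an analysis plan. This stands in part: a baseline-only reading is open. But the article does state a rule, attaches it to a data source described as spanning the study, and sets no limit. That is a loosely fixed rule, not merely an omitted detail.

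Four stronger readings are tempting and not supported:

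- *That the plan definitely adjusts for follow-up services.* No time point is given.
- *That {20a} and {20b} are two rival primary models.* {20a} names the analysis of primary interest, and {20b} is headed as additional analyses. Its sentence can also be read as saying that those analyses which are adjusted will be intention-to-treat. {20a} does not say its list of fixed effects is exhaustive. What remains is unclear scope.
- *That the intervention changes services, so that adjusting the H4 analysis nearly conditions on its outcome.* Setting up contact is conditional and covers an unknown share of participants, and H4 is a hypothesis. The outcome table assigns needs to a separate instrument, the NPCS, and its overlap with the ICSO-R variables is not shown.
- *That the trial loses a known amount of power.* With 54 per group, Φ(d√27 − 2.241) gives 0.81 at d = 0.60, 0.76 at 0.57 and 0.36 at 0.36. The last two values rest wholly on the assumed mediation figures and ignore the opposite bias.

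**Conclusion.** The point holds as a defect of wording with a real statistical consequence. As written, the rule permits intention-to-treat analyses to be adjusted for service variables that treatment may have changed. The resulting bias can go either way, so the adjustment cannot be defended as conservative. Its size cannot be derived from the documents; the figures above only show that it need not be trivial against a planned effect of 0.6 SD.

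The conclusion depends on two things the article leaves open: whether post-randomisation values would be used, and whether the primary model is included. If only T1 values are meant, the bias disappears and the remaining defect is that this is not said. The sample size is not in question.

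**What to change.** - In {20a}, state that the mixed model described there is the primary intention-to-treat analysis, and whether it carries covariates.
- In {20b}, state that any adjustment uses only named variables measured at T1 before randomisation: sociodemographic variables and, if wanted, T1 service use. Say which analyses are adjusted.
- State that follow-up ICSO-R data serve only to describe care received, for costing, or in a mediation analysis labelled exploratory.

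The cost is a few sentences in the protocol or analysis plan, ideally settled before unblinded analysis. No new data are needed, T1 service use is already collected, and 60 per arm stands.
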